### Power analyses

To estimate the sample size needed to detect statistically significant differences between TEAMS groups in the context of the 3-level nested data structure (e.g., aim 1, hypothesis 1), the power program RMASS2 [109] was used. The RMASS2 program is specifically designed to calculate the projected sample size needed for longitudinal data with attrition when a comparison is made between groups. To determine the minimum sample size necessary, several assumptions were made: (1) An alpha level of .05 and a power level of 0.80, (2) an effect size of *d* = .39 (based on the CPRT effectiveness trial ES for impact of training on teacher fidelity), (3) 30% overall attrition rate was specified, and (4) a stationary autoregressive structure (lag 1) was specified for the variance-covariance matrix of the repeated measures, using an autocorrelation value of 0.60. In addition, clustering at the programs/districts level was accounted for via the variance inflation factor (VIF = 1.28): 1 + (*c* − 1) × ICC, where *c* is the average number of providers/children per programs/districts (*n* = 8) and the ICC at the programs/districts level (ICC = 0.04, based on AIM HI therapist fidelity outcome). Given these assumptions, 502 providers/children nested within 63 programs/districts are needed to detect statically significant differences between at least two of the TEAMS intervention groups.

Additional power analyses were conducted to determine the sample size needed to detect a hypothesized mediated effect or moderation of the antecedent to mediator relationship (see Aim 3), which is likely to be the most underpowered effect proposed. This set of power analyses was conducted to determine the minimum necessary sample size to find a statically significant mediated effect from variables presenting the TEAMS groups to a target mediator (e.g., provider attitudes) to a target outcome (e.g., provider fidelity outcome). Using the simulation approach for meditational models of Thoemmes, MacKinnon, and Reiser [110], small effects (*R*^2^ values of 2%) were specified for both the mediator and outcome variables. Accounting for the VIF defined above, 591 providers/children nested within 74 programs/districts are needed to detect statistically significant mediated effect.

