**Fig. 3 Fig3:**
[figure not shown]
TEAMS consort diagram

A dismantling design will be used to understand the effectiveness of TEAMS and the mechanisms of change across settings and participants [89]. The specific aims and hypotheses are to:Test the effectiveness of the TEAMS modules individually and in combination on implementation outcomes when paired with two ASD EBI. (a) Compared to standard ASD EBI training (control) and individual TEAMS modules (TLI or TIPS), the full TEAMS model (TLI + TIPS) will lead to more positive implementation outcomes for providers (training completion, fidelity) and children (improvements in targeted symptoms).Test the impact of TEAMS modules on organization- and provider-level mechanisms of change. (a) TLI will increase use of implementation leadership strategies, and TIPS will lead to greater changes in provider attitudes and engagement in EBI training.Identify moderators and mediators of implementation outcomes. (a) Identify provider and organization characteristics that moderate implementation outcomes and (b) identify provider- and leader-level mechanisms of change that mediate implementation outcomes.

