#### Provider fidelity measures

Provider ASD EBI (AIM HI/CPRT) fidelity is the primary study outcome. Provider fidelity will be based on ratings by trained observers blind to study condition and time frame. Fidelity ratings are designed to capture provider use of the core EBI strategies included in the AIM HI and CPRT protocols. Fidelity will be rated with the target child at PRE, mid training, and POST. Fidelity will be coded based on video recordings of sessions/activities using our established procedures for video data collection. AIM HI Fidelity includes 16 Adherence items reflecting expected within-session therapist behaviors in three categories (Structuring Sessions for Skill-Building, Motivating Children, Active Teaching). These are rated separately for parents and children. There are also 4 Effectiveness Items (e.g., session is organized and structured). The inter-rater reliability of these items are high (*M* = .77, range = 0.65 to 0.90 based on 299 double-coded sessions). Furthermore, all individual and composite scores for therapists trained in AIM HI are significantly higher than therapists delivering usual care (based on over 600 coded sessions), providing support for the discriminant validity of the measure. Sessions recordings will be submitted online prior to training and monthly during the 6-month training/consultation period*.* CPRT fidelity includes 15 adherence items reflecting expected within-session teacher behaviors in three categories (maximizing student motivation, facilitating student responding, providing appropriate consequences). There are also 4 effectiveness items (e.g., manages distractions in the teaching environment). All items are rated on a 1–5 Likert scale after observing the complete activity with 1 being teacher does not implement or implements correctly less than 30% of the time to 5, teacher implements correctly throughout the session (100%). The inter-rater reliability of these items are high (*M* = .73, range = 0.50–0.90 based on 240+ double-coded sessions).

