## Data analysis

### General data analytic plan for aims 1–3

All data analytic strategies will follow the recommendations of Brown et al. and the Prevention Science and Methodology Group for randomized field trials [103]. Preliminary data screening and cleaning will require examination of the data distributions for normality and missing data patterns at both the univariate and multivariate level. Preliminary data analysis will also be conducted to determine if there are significant differences between the two studies (CPRT and AIM HI) on target variables. If no significant differences are found, data from the two studies will be integrated to maximize the available data for specific analyses. In the case that outcome variables differ by study, variables representing study will be included as a covariate in all models. Some of the target outcome variables in the two studies were measured using different scales (e.g., AIM HI and CPRT Fidelity). To ensure comparability on these measures, variables will be converted to *z*-scores before statistical comparisons are made. Hierarchical linear modeling (HLM) will be used as the primary, but not only, statistical model due to the nested structure of the data and when the outcome measure is at the provider/outcome level: repeated measures [level-1] nested within providers/children [level-2] nested within program/district [level-3]). Possible clustering effects will initially be estimated by examining intraclass correlation coefficients to determine if accounting for clustering is necessary. All analyses will use an intent-to-treat approach for the TEAMS groups. Because the TEAMS condition variable will contain four groups, three dummy-coded variables will be created and used as predictor variables in target statistical models. To account for the different type of leader at the program/district level, a level-3 binary variable representing whether or not the agency/district leader is a director or a first-level leader will be used in all analyses. Covariates (e.g., baseline scores) may be included in the models to adjust for nonequivalence at baseline and to minimize bias. All analyses will use AR(1) to model a first-order autoregressive correlation structure for the repeated-measures data. Missing data common to longitudinal designs is readily incorporated in HLM if the data can be assumed to be missing at random. However, because there is no statistical test of data that is missing at random [104], all data analysis will also employ selection models [105] to model relationships of interest for the data missing not at random mechanism, as recommended by Little and Rubin [106]. Of interest in some of proffered hypotheses are the differences in target outcomes between the TEAMS groups over time. The TEAMS groups will be statistically compared when a significant cross-level (Time X TEAMS Group) interaction is evident using the statistical methods of Preacher, Curran, and Bauer [107].

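### The 80% power stated for aim 1, hypothesis 1 belongs to one pairwise contrast; hypothesis 1a needs three, with power of about 61% at 502 providers and 71% at 590

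*Protocol article*

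**What the plan says.** The aims in the protocol article (Background, Current project) compare the combined arm with control and with each single module: "the full TEAMS model (TLI + TIPS) will lead to more positive implementation outcomes for providers". For a given outcome that is three contrasts, all involving the TLI+TIPS arm. Provider fidelity is named as the primary outcome.

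The first paragraph of Power analyses gives aim 1, hypothesis 1 as the example of what it sizes. It assumes "An alpha level of .05 and a power level of 0.80", "an effect size of *d* = .39", that "30% overall attrition rate was specified", and a first-order autoregressive structure "using an autocorrelation value of 0.60". It adds a variance inflation factor of 1.28 for clustering and arrives at 502 providers in 63 programs/districts. The event to be detected is described as being able to "detect statically significant differences between at least two of the TEAMS intervention groups".

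The general data analytic plan enters condition as three dummy variables and sets a condition on group comparisons: "The TEAMS groups will be statistically compared when a significant cross-level (Time X TEAMS Group) interaction is evident". The aim 1 analysis section refers to main effects, interactions and group differences. It does not say which pattern of results supports 1a.

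The Sample section sets enrolment at 590 providers in 74 programs/districts and gives the aim 3 mediation analyses as the reason.

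**The concern.** A difference between at least two of four arms can arise from any of six pairs. Three of those pairs (TLI versus standard, TIPS versus standard, TLI versus TIPS) say nothing about whether the combination is better. The stated 80% is therefore attached to an event that is not hypothesis 1a.

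This matters most in a dismantling design, whose purpose is to separate three conclusions: TEAMS works, one module is enough, or the combination is needed. A reader of the power section would expect an 80% chance of confirming 1a under the planning effect. If the real chance is well below that, failing to beat one of the single modules is a likely result even when 1a is true, and could be misread as evidence that the combination adds nothing.

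The interaction gate adds to the problem. It places an extra test in front of contrasts that the hypothesis already names.

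**Working it through.** **Inputs.** From Power analyses: alpha .05, power .80, d = .39, attrition 30%, AR(1) correlation .60, ICC .04, 8 providers per cluster. From Provider fidelity measures: three observations ("Fidelity will be rated with the target child at PRE, mid training, and POST"). Assumed, because not stated: two-sided testing, equal allocation to four arms, a normal approximation, and the same attrition and clustering in every arm.

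**Step 1: reproduce the 502.**
- One contrast, one observation: n per arm = 2(1.96 + 0.842)² / 0.39² = 103.2.
- Variance factor for three AR(1) observations at .60: generalised least squares (1 + .6) / (3 − .6) = 0.667; simple mean [3 + 2(2 × .6 + .36)] / 9 = 0.680.
- Clustering: 1 + (8 − 1) × 0.04 = 1.28.
- Total: 103.2 × 0.667 × 4 × 1.28 / 0.70 = 503, or 513 with 0.680. Stated: 502.

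Variants that miss: one-sided .05 gives 396 to 404; four observations give 431 to 447; one observation gives 755; multiplying by 1.3 for attrition instead of dividing by 0.70 gives 458 to 467. The 502 thus matches one pairwise contrast at an undivided two-sided .05.

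**Step 2: power for all three contrasts.** At N = 502 one contrast has expected z = 1.96 + 0.842 = 2.80. At 590 it is 2.80 × √(590/502) = 3.04. Four independent arm estimates of equal precision were simulated (1,000,000 draws). A success required full TEAMS to exceed every other arm with z > 1.96.

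| True pattern | N | Full vs standard | Full beats all three |
|---|---|---|---|
| Full exceeds each other arm by d = .39 | 502 | 80% | 61% |
| Same | 590 | 86% | 71% |
| Each module has half the effect (assumption) | 502 | 80% | 14% |
| Same | 590 | 86% | 18% |

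In the half-effect pattern, full TEAMS against a single module has power of only 29% (502) or 33% (590), which is what drives the low figures. For scale, 80% power for all three under the first pattern would need about 697 providers.

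**Step 3: false-claim rate if all three are required.** This is an intersection-union test. The rate is 0.16% when all arms are equal. It reaches 2.5% in the worst case, where full equals one module and both far exceed the other two arms. No division of alpha is needed.

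**Step 4: the gate, read as a 3-df test at .05.** The gate was applied to the same simulated arm estimates, using the chi-square critical value on 3 df.
- Only the full arm works, N = 502: full versus standard falls from 80% to 74%.
- Each module has half the effect, N = 502: it falls from 80% to 63%.
- Only the full arm works: a false difference among the other three arms, all truly equal, still appears in about 12% of trials.
- When all four arms are equal, the gate holds the chance of any pairwise finding at 5.0%. Its protection is limited to that case.
- The all-three claim hardly changes (61.2% to 60.5% at 502 when only the full arm works), so for 1a itself the gate adds little.

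**The case against.** **This is a hypothesis and a power target, not two success rules.** That is right. Neither section says when 1a will be claimed. A reader might infer from the at-least-two-groups wording that any significant pair could be reported as support for the full model, and so that unadjusted testing inflates false claims of 1a. The article does not say this. Taken as written, 1a requires all three contrasts, and step 3 shows that this rule keeps the error at 2.5% or less at full alpha. The problem is power.

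**The SAP may hold the multiplicity scheme.** This also stands. The absence of an alpha allocation in a condensed article is not a fault, and the form of the interaction test may be defined elsewhere. What remains is what the article does state: a sample size tied to aim 1, hypothesis 1 that was calculated for something else, and a significant interaction as the condition for comparing groups.

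**Enrolment is set by aim 3, so the 502 does not bind.** Partly right. The planned 590 raises power for 1a, but only to about 71% in the more favourable of the two patterns examined.

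**The gate protects against error.** It does so when all four arms are equal. Once one arm differs it no longer protects the remaining pairs, and it takes power from the leading contrast.

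**Conclusion.** The point holds as a mismatch between hypothesis and power. The 80% at 502 providers describes one pairwise contrast. For hypothesis 1a, power is about 61% at 502 and 71% at 590 if full TEAMS exceeds each other arm by d = .39, and about 14% and 18% if each single module has half the effect. The half-effect pattern is an assumption used for illustration; the article gives no expected effect for the single modules.

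The gate is a lesser, related fault. As a 3-df test it lowers full-versus-standard power to 74% at 502 when only the full arm works, and leaves about a 12% chance of a false difference among the other arms.

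The documents do not support the stronger inference that the plan allows 1a to be claimed falsely at an inflated rate, because no section states a rule that accepts a partial pattern.

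The figures rest on two-sided tests, equal arms, a normal approximation, and the article's own effect size, attrition and clustering. They take the stated 80% for one contrast at face value, with the difference constant over the three observations, and the gate is evaluated on the same arm estimates.

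**What to change.** 1. In Power analyses, replace the at-least-two-groups wording with the single contrast to which the 502 refers. State the power for hypothesis 1a at 502 and at 590, with the effects assumed for the single modules.
2. State that 1a is claimed for fidelity only if TLI+TIPS is significantly better than standard training, than TLI and than TIPS, each at two-sided .05. No alpha split is needed.
3. Test these three pre-named contrasts without first requiring a significant Time x Group interaction.
4. Label the other three pairs as supportive, or adjust them by Holm's method.

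**Cost.** The changes are to the text; no extra data or enrolment is proposed. The price is a less favourable stated power for 1a, a harder claim that the combination beats each module, and a lower standing for the other pairwise results. Dropping the gate also gives up its protection when all arms are equal. For 1a the all-three rule replaces that protection; for the other pairs, the supportive label or Holm adjustment has to do so.

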### Sample

The combined multi-level sample for both studies will include 74 programs/districts, 74 agency/district leaders (1 per agency/district), 590 providers (average of 8 per program/district), and 590 children (1 per provider). This sample size was determined so as to be sufficiently powered for aim 3 mediation analyses. (Refer to Table 1 for the breakdown of participants by study and type).

**Table 1 Tab1:** Participants by type and study

AIM HI study (37 MH programs)	CPRT study (37 school districts)	Combined (74 agencies)
37 Program managers	37 Program specialists	74 Leaders
295 Therapists	295 Teachers	590 Providers
295 Clients	295 Students	590 Children
*627 Total AIM HI*	*627 Total CPRT*	*1254 Total Combined*

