#### Specific analyses for aim 2: test the impact of TEAMS modules on leader- and provider-level mechanisms of change

Measurement of leader-level outcomes is of primary interest. Implementation Leadership and Climate scores will be aggregated to the leader level. For this reason, HLM models (or single-level regression models if ICC values suggest clustering is negligible) will be used to test for TEAMS group differences on measures of implementation leadership and climate scores at 6 and 12 months. These analyses will control for baseline scores on these measures. To determine if there are significant differences between the TEAMS groups on therapist attitudes (EBPAS), analyses will proceed using the 3-level nested data structure outlined in the General Analytic Plan. These analyses will control for baseline EBPAS scores.

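### The 591-provider, 74-cluster power figure does not cover leader-level effects (aim 2 leadership and climate tests, aim 3 mediation through them), which rest on 74 leaders

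*Protocol article*

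**What the plan says.** The Power analyses section of the protocol article gives two calculations, both counted in providers/children with a variance inflation factor of 1.28 from the fidelity ICC of 0.04. The first gives 502 for aim 1, with d = .39 ("based on the CPRT effectiveness trial ES for impact of training on teacher fidelity"). The second gives 591 in 74 programs/districts for an aim 3 mediated effect, with R² of 2% for both mediator and outcome, provider attitudes as the example mediator and provider fidelity as the example outcome. It calls the mediated or moderated effect the one "which is likely to be the most underpowered effect proposed".

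The Sample section takes N from the second calculation: "This sample size was determined so as to be sufficiently powered for aim 3 mediation analyses". It also gives the number of leaders: "74 agency/district leaders (1 per agency/district".

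Under the specific analyses for aim 2, "Measurement of leader-level outcomes is of primary interest" and "Implementation Leadership and Climate scores will be aggregated to the leader level". Group differences are tested at 6 and 12 months with control for baseline. Under aim 3, implementation leadership and implementation climate appear alongside provider attitudes as mediators. The general analytic plan codes the four conditions with three dummy variables. No effect size, power or detectable difference is given for any leader-level test.

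**The concern.** By presenting 591/74 as the figure for the weakest effect, and as sufficient for aim 3 mediation, the plan invites the reader to take the remaining effects as adequately powered. For effects analysed at the leader level that does not follow. There are 74 records, about 18.5 per arm, and adding providers within a program adds no leaders. The 1.28 inflation factor does not help, because both the randomised condition and the aggregated score sit at the leader level.

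Separating what leader training adds from what provider training adds is the purpose of the dismantling design. A reader relying on the power section could take a non-significant TLI difference on leadership or climate as evidence that TLI does not move its own target, when the design would often miss a small-to-moderate effect.

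**Working it through.** **Inputs from the protocol:** "An alpha level of .05 and a power level of 0.80"; R² = 2% for mediator and outcome; ICC .04; 8 providers per cluster; VIF 1.28; 74 leaders. **Assumed:** two-sided test, equal allocation (37 v 37 for TLI v no TLI, 18.5 v 18.5 for a pair of arms), no loss of leaders unless stated, baseline correlation r, and leadership/climate ICCs other than .04.

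**1. The plan's figure.** VIF = 1 + (8 − 1) × .04 = 1.28. 591 / 1.28 = 461.7, so 462 independent providers. A single-level mediation simulation with both paths at R² = 2% and a bias-corrected bootstrap gives 79% power at n = 462. 462 × 1.28 = 591.4, and 591 / 8 = 73.9, so 74 clusters. The figure is right for a mediator measured on each provider.

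**2. The same effect at leader level.** For a balanced two-group contrast, d = 2√(R²/(1 − R²)) = 2√(.02/.98) = .286. Power is from the noncentral t with the four-group residual, df = 70.

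- TLI v no TLI: ncp = d√74/2 = .286 × 4.301 = 1.23, power 23%. Detectable d at 80% power is .66.
- Any two arms: ncp = d√(18.5/2) = .286 × 3.041 = .87, power 14%. Detectable d is .93.

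**3. Baseline adjustment.** The SD is multiplied by √(1 − r²). At assumed r = .6 this is .8.

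- TLI v no TLI: power 33%, detectable d = .66 × .8 = .53.
- Any two arms: power 19%, detectable d = .93 × .8 = .75 (from unrounded values).
- Over r = .5 to .7, TLI v no TLI power is 29% to 40%.

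**4. At the aim 1 effect, d = .39.** TLI v no TLI has 38% power unadjusted, and 48% to 64% with r = .5 to .7.

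**5. Mediation through a leader-level score.** Simulation: 74 clusters of 8, mediator at leader level, outcome ICC .04, joint-significance test. At d = .286 the TLI-to-mediator path alone has 23% power, the mediator-to-outcome path 84%, and the mediated effect 19%. At d = .39 the mediated effect has 32%.

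**6. Effect in provider SD units.** If scores are means of 8 provider ratings, SD of the mean = √(ICC + (1 − ICC)/8).

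| ICC | SD of mean | .286 / SD | Power, TLI v no TLI |
|---|---|---|---|
| .04 (fidelity value) | .40 | .71 | 86% |
| .1 (assumed) | .46 | .62 | 75% |
| .2 (assumed) | .55 | .52 | 60% |
| .4 (assumed) | .69 | .41 | 42% |

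For a pair of arms, power is 57% even at ICC .04.

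**7. Leader attrition.** The aim 1 calculation states that "30% overall attrition rate was specified". If that also applied to leaders (assumed; 74 × .7 ≈ 52, unadjusted), detectable d would be .79 for TLI v no TLI and 1.12 for a pair of arms.

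**8. What a null could exclude.** The unadjusted 95% CI half-width for TLI v no TLI is 1.994 × √(2/37) = .46 SD, or .46 × .8 = .37 at r = .6. For a pair of arms it is 1.994 × √(2/18.5) = .66 SD. At d = .8, TLI v no TLI power is 92%.

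**The case against.** Three stronger readings are tempting, and the protocol does not support them.

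**That the plan ranks mediation wrongly.** A reader might infer that aim 2 is weaker than mediation as a class. It is not. Leadership and climate are themselves aim 3 mediators, and a mediated effect through them contains the aim 2 path, so it is weaker still (19% against 23%). The plan also hedges with a word of likelihood. The fault is that 591 was worked out for a provider-level mediator and presented without that limit, so deleting the ranking would be the wrong repair.

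**That a null in aim 2 would be uninformative.** With a half-width of about .46 SD, a null near zero would exclude large effects. It would leave small-to-moderate ones open.

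**That leader-level outcomes are primary for the trial.** The phrase about primary interest applies within aim 2. The section on provider fidelity measures makes fidelity the primary study outcome.

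Other objections stand in part. No expected TLI effect on leadership is stated. R² = 2% and d = .39 come from calculations about provider-level quantities, while TLI trains leaders directly and may do better. The provider-unit result at ICC .04 exceeds 80%, but that ICC belongs to fidelity; nothing in the protocol supports it for ratings of a shared leader and climate. Three dummy variables do not name a pooled TLI v no TLI contrast, so the more favourable figures belong to a test the plan has yet to specify. The hypothesis about leadership strategies also has a separate measure of implementation support strategies, so it does not rest on leadership and climate scores alone.

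A condensed article may leave secondary power figures to a fuller document. Here, though, the article states what its N covers, and that statement is too wide.

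**Conclusion.** The concern holds in limited form. The 591/74 figure is correct for a mediator measured on each provider and does not extend to effects analysed on 74 leaders. At the plan's own small effect, in leader-level SD units and unadjusted, those effects have 14% to 23% power where the calculation that set N has about 80%. Baseline adjustment at r = .6 lifts the two aim 2 contrasts to 19% and 33%.

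The size of the shortfall depends on assumptions that the protocol does not settle: the scale of the effect, the ICC of leadership and climate ratings, the baseline correlation, equal allocation, and leader retention. Only provider SD units combined with the fidelity ICC bring TLI v no TLI above 80% at this effect. The aim 1 calculation and the status of fidelity as primary outcome are unaffected.

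**What to change.** **Sample and Power analyses sections:** limit the 591/74 statement to mediators measured at provider level. Add, with the assumptions named, that leader-level tests rest on 74 leaders and have 80% power for d of about .66 for TLI v no TLI (about .53 if baseline correlates .6 with the outcome) and about .93 (.75) between any two arms. Say that mediation through leadership or climate is no better powered than the leader-level path it contains.

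**Specific analyses for aim 2:** name the contrast of both TLI arms against both non-TLI arms as the aim 2 test of TLI on leadership and climate, alongside the dummy-coded comparisons. Report it with a 95% confidence interval, and state that a non-significant result does not exclude small-to-moderate TLI effects.

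**Cost:** wording in three sections and one named contrast on data already planned. A stated property of the design becomes less favourable. No added sites, participants or measurements.

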#### Specific analyses for aim 3: identify moderators and mediators of implementation outcomes

Variables representing participant characteristics (e.g., job tenure, gender, race/ethnicity) and organizational characteristics (e.g., size) will be evaluated as moderators of the relationship between the dummy-coded TEAMS group variables and outcome variables specified in aim 1. All analyses will proceed as specified in aim 1 above. Relevant interaction terms between the TEAMS group variables and a given moderator will be created and entered as predictor variables. Two sets of models will be used: one set for provider-level outcomes and a second for child-level outcomes. To examine the hypothesized mediated effects of TEAMS group status on fidelity and child outcomes, multilevel path analysis will be conducted. Measures of provider attitudes, implementation leadership and implementation climate will be tested as mediators in respective models. The specific mediated effects within these models will be tested using the bias-corrected bootstrap approach [108].

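### The aim 3 sample size of 591, on which the trial is sized, contains no allowance for the 30% attrition assumed for aim 1, and it does not cover leadership and climate mediators if these are analysed at leader level

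*Protocol article*

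**What the plan says.** The Sample section plans 74 programs/districts, one leader in each, and 590 providers with one child each. It justifies the number thus: "This sample size was determined so as to be sufficiently powered for aim 3 mediation analyses".

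The Power analyses section has two calculations.

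- **Aim 1.** The listed assumptions include "1) An alpha level of .05 and a power level of 0.80", d = 0.39, "3) 30% overall attrition rate was specified", an autocorrelation of 0.60 and a VIF of 1.28 (8 per cluster, ICC 0.04 from AIM HI therapist fidelity). The result is 502 in 63 clusters.
- **Aim 3.** Small effects (R² "values of 2%) were specified for both the mediator and outcome variables") go into a simulation whose example is provider attitudes acting on provider fidelity. The only adjustment named is the VIF: "Accounting for the VIF defined above, 591 providers/children nested within 74 programs/districts are needed to detect statistically significant mediated effect".

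The aim 3 analysis section specifies multilevel path analysis with a bias-corrected bootstrap and lists the mediators: "Measures of provider attitudes, implementation leadership and implementation climate will be tested as mediators in respective models". The aim 2 analysis section says of two of them: "Implementation Leadership and Climate scores will be aggregated to the leader level".

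**The concern.** Attrition is built into the smaller requirement (502) and is not mentioned in the larger one (591), which fixes the size of the trial. Enrolment is set at 590, one below the stated minimum, so any loss takes aim 3 under its own requirement.

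A second gap concerns scope. The VIF of 1.28 comes from a provider-level fidelity outcome. It does not describe a mediator that takes one value per cluster in a trial that randomises clusters. Leadership and climate are the route through which the leadership module is expected to work, so the power claim matters for that half of the mechanism question. A reader who relies on the stated sufficiency could give a null mediation result more weight than the design supports.

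**Working it through.** **Inputs.** From Power analyses: VIF = 1 + (8 − 1) × 0.04 = 1.28; R² = 2% for mediator and outcome; attrition 30% (listed for aim 1 only). From the aim 3 analysis section: bias-corrected bootstrap. From Sample: 590 providers, 74 clusters. Two-sided alpha 0.05 and power 0.80 are stated for aim 1 and assumed to carry over to aim 3.

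**1. Reproduce 591.** 591/1.28 = 461.7. A single-mediator model was simulated with R² = 2% per path (coefficient √(0.02/0.98) = 0.143 against unit residual variance), no direct effect, and 1,500 replicates (Monte Carlo standard error about 0.01). At n = 462 with complete data, power is 0.80–0.81, and 462 × 1.28 = 591.4. The figure is reproduced with no attrition term.

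**2. Could attrition already be inside 591?** The base would then be 591 × 0.7/1.28 = 323, where simulated power is only about 0.60. That does not match a target of 0.80.

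**3. Compare aim 1.** Take the mean of three measures with AR(1) correlation 0.6. Its variance factor is (3 + 2 × (0.6 + 0.6 + 0.36))/9 = 0.68. Per group, n = 2 × (1.96 + 0.8416)² × 0.68/0.39² = 70.2. Four groups times 1.28 gives 359 without attrition. Dividing by 0.7 gives 513. The stated 502 is within about 2% of the version with attrition. This only approximates the plan's own software.

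**4. Power at the planned 590, provider-level mediator.** The effective n is given with the VIF kept at 1.28, and with the VIF recomputed for the smaller clusters.

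| Effective loss | Remaining | Mean per cluster | VIF recomputed | Effective n | Power |
|---|---|---|---|---|---|
| 30% | 413 | 5.6 | 1.184 | 323–349 | about 0.60–0.66 |
| 20% (assumed) | 472 | 6.4 | 1.216 | 369–388 | about 0.71 |
| 15% (assumed) | 501.5 | 6.8 | 1.232 | 392–407 | about 0.72–0.76 |

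Individual simulation runs scatter by one or two points around these values.

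**5. Leadership and climate as leader-level aggregates.** The path from group to mediator then has 74 observations.

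- R² needed for 80% power on that path: (1.96 + 0.8416)²/74 = 0.106, so R² = 0.106/1.106 = 9.6%; with the noncentral t, 9.8%.
- If the 2% is the R² of the cluster-level score, power is 0.23.
- If the 2% refers to individual ratings, averaging m raters raises it to R² = 0.02/(0.02 + 0.98 × (ICC + (1 − ICC)/m)). The rating ICC is not in the document, so a range is assumed:

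| Rating ICC (assumed) | m = 8: R², power | m = 5.6: R², power |
|---|---|---|
| 0.04 | 11.3%, 0.86 | 8.8%, 0.75 |
| 0.10 | 8.8%, 0.75 | 7.3%, 0.66 |
| 0.20 | 6.4%, 0.60 | 5.6%, 0.54 |
| 0.30 | 5.0%, 0.50 | 4.6%, 0.46 |

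These figures are for the first path only. The mediated effect also needs the second path: with a first-path R² of 10% and 2% on the second, a cluster-level simulation gave 0.63 by joint significance.

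**The case against.** **Partial data.** Fidelity is observed three times, the multilevel models use incomplete records under missing at random, and the 30% is an overall rate. The information lost may therefore be smaller than a completers-only count implies. This stands, and it is why the 15–20% rows are given. It does not rescue the claim: providers who leave still take their post-training mediator and outcome values with them, and 590 leaves no margin.

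**Leader-level power.** A reader might infer that leadership and climate mediation has only about a one-in-five chance of detection and is therefore shown to be underpowered. The document does not support that. The 2% is set with provider attitudes as the example, and no cluster-level effect is given for leadership or climate. Table 3 has both scales completed by leaders and providers, so an aggregate averages several raters and can have an R² well above 2%. The aggregation is stated under aim 2. Aim 3 does not give the mediator's level, so a provider-level analysis remains possible. What stands is that the 591 calculation does not address a leader-level aggregate.

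**Importance.** Fidelity is the primary outcome, and its requirement of 502 already includes attrition and lies below 590. The Power analyses section itself calls the mediated or moderated effect the one most likely to be underpowered. Both points are right and limit the reach of the finding. They do not make the sufficiency statement in the Sample section correct.

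**Conclusion.** The concern holds for the aim 3 sample size. On the plan's own inputs, 591 is a complete-data requirement of about 462 multiplied by 1.28. With 590 enrolled, power for a provider-level mediator is about 0.60–0.66 under the plan's 30% loss and about 0.71–0.76 under an assumed effective loss of 15–20%, against a target of 0.80. This rests on alpha 0.05 and power 0.80 carrying over from aim 1, on R² = 2% per path in a single-mediator model, and on the bias-corrected bootstrap.

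For leadership and climate the conclusion is narrower. If they are analysed as leader-level aggregates, the stated calculation does not apply to them. First-path power then lies anywhere between about 0.23 and 0.86, depending on what the 2% means and on a rating ICC the document does not give. A shortfall is plausible there but not established.

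The aim 1 comparison is not affected.

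**What to change.** Three changes of wording, with no added recruitment:

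1. In Power analyses, say that 591 assumes complete data. Give aim 3 power at 590 for provider-level mediators: about 0.60–0.66 if 30% contribute no mediator or outcome data, and about 0.71–0.76 if the effective loss is 15–20%, labelled as an assumption.
2. In Sample, qualify the statement that the size is sufficient for aim 3 accordingly.
3. State the level at which leadership and climate enter the mediation models. If it is the leader level, add a separate power statement on 74 clusters: R² of about 10% for 80% power on the group-to-mediator path; power of about 0.23 if the cluster-level R² is 2%; about 0.46–0.86 if 2% refers to individual ratings, with an assumed rating ICC of 0.30 down to 0.04 and 5.6 to 8 raters per cluster.

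Labelling leader-level mediation as exploratory is optional. Restoring 80% power under full 30% loss would take 591/0.7 = 845 providers, about 106 clusters at 8 each. That is not proposed.
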